## Abstract

**Objective:**

Autism spectrum disorder (ASD) is a neurodevelopmental condition with limited effective treatment options, including Applied Behavior Analysis, Transcranial Magnetic Stimulation, and certain medications aimed at managing associated behavioral and emotional regulation challenges. Primary interventions include educational training and behavioral modifications. However, long-term, intensive, and individualized rehabilitation training strategies are lacking, and new rehabilitation tools therefore urgently need to be developed. Virtual reality (VR) is a promising digital rehabilitation tool that may support the development of essential life skills, such as social communication and daily living abilities, in many children and adolescents with ASD. Herein, we introduce a protocol for an initial multicenter randomized controlled trial focused on preschool-aged children with ASD. This trial aims to investigate the clinical efficacy of behavioral training for young children with ASD utilizing VR technology.

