**Figure 1 f1:**
[figure not shown]
Protocol flow chart of the study. ABC, Autism Behavior Checklist; CARS, Child Autism Rating Scale; SDQ, Strengths and Difficulties Questionnaire; ADOS, Autism Diagnostic Observation Schedule; fNIRS, functional Near-Infrared Spectroscopy.

Participants were enlisted through advertisements in outpatient clinics, kindergartens, community bulletins, and social media platforms. Overall, 160 children aged 4–7 years who met the criteria for ASD, according to the criteria outlined in the Diagnostic and Statistical Manual of Mental Disorders, Fifth Edition (DSM-5), were enrolled. The formal diagnosis was determined using the gold standard instrument, the Autism Diagnostic Observation Schedule, Second Edition (ADOS-2), alongside clinical judgment by experienced psychologists. All participants were between the ages of 4 and 7 years old. Only children who satisfied the eligibility criteria (IQ score of at least 70) for the study were enrolled after completing the Wechsler Preschool and Primary Intelligence Scale (Chinese version) assessment, administered by a professional clinical psychologist. The randomization process was performed using SAS software (version 9.4, SAS Institute).

The primary objective of this study was to create and apply a behavioral training system using VR technology for preschool children with ASD. This system comprises a program utilizing VR technology, a real-time computer monitoring system, and a cloud-based management system. Participants in either the experimental or control group will receive 24 sessions of the intervention model (two sessions per week for 12 consecutive weeks). Participants will be assessed at six time points as follows: before the start of treatment; at 8, 12, and 16 weeks during the treatment period; and at 24 and 32 weeks following the completion of the intervention. The evaluation will follow the guidelines of good clinical practice. The assessment will include questionnaire scales completed by parents, observational scales administered by clinicians, and quantitative fNIRS to measure changes in hemoglobin (Hb) concentration at rest. These include indicators of training, behavioral symptoms, symptom severity, prosocial behaviors, and brain functioning.

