### Sample size calculation

2.2

The sample size was determined based on the primary outcome measure and the scores from the ADOS scale. Previous studies reported an average ADOS-2 score of 16.9 ± 4.1 for children with ASD (25). In this study, we hypothesized a clinically meaningful difference of 2 points in the intervention group compared to the control group, indicating the efficacy of the VR-based intervention. The required sample size was calculated using the PASS 15.0 software, with the stipulation of α=0.05 and the test efficacy 1-β=0.8. This process yielded a sample size of 72 patients. Given a 10% loss of visits, the calculated sample size for each group was 80, with a total sample size of 160 cases.

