Data analyses will be performed using SPSS software (version 26; IBM Corp.). Paired-sample t-tests will be employed to assess for pre- and post-treatment comparisons between normally distributed measures. Similarly, the Kappa consistency test will be used to perform pre- and post-comparisons of count data. Independent sample t-tests will be employed for between-group comparisons of normally distributed measures, while nonparametric tests will be utilized for between- and within-group comparisons of non-normally distributed measures. Repeated ANOVAs will be conducted to evaluate the treatment effects within each group. The goal of this study is to identify any differences in variables between baseline and post-test measurements in both the treatment and control groups. The factors considered include time (before and after) and group (experimental vs. control), with each measure serving as a dependent variable. For measures that meet the normality test, means ± standard deviation will be used to describe results. Conversely, medians and percentiles will be employed for measures that do not meet the normality test. Count data will be presented as the median and interquartile range. Statistical significance will be defined as a p-value of 0.05 or less. To manage missing outcome data, we will assume that data are missing at random and will apply multiple imputation as the primary approach. Bonferroni correction adjustments will be applied where appropriate to control for the risk of Type I error due to multiple comparisons.

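### The plan assigns evaluation of treatment effects to within-group ANOVAs and does not say which between-group contrast tests efficacy or adjust it for baseline

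*Protocol article*

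**What the plan says.** Section 3 (Statistical analysis) of the protocol article lists several analyses side by side.

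- **Within group:** paired t-tests for before-after change, nonparametric equivalents for non-normal measures, and "Repeated ANOVAs will be conducted to evaluate the treatment effects within each group". The next sentence sets the goal as finding baseline to post-test differences in both arms.
- **Between groups:** "Independent sample t-tests will be employed for between-group comparisons of normally distributed measures, while nonparametric tests will be utilized" for the non-normal ones.
- **Layout:** "The factors considered include time (before and after) and group (experimental vs. control"), with each measure as a dependent variable.

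The section does not name the time-by-group interaction, does not say which of these analyses decides efficacy, and names no baseline covariate.

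Section 2.1 (Study settings) says "Participants will be assessed at six time points as follows": baseline, weeks 8, 12 and 16, then weeks 24 and 32. Section 4 (Discussion) assigns the last two to showing whether effects are maintained.

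Section 2.2 (Sample size calculation) plans for a between-group difference in ADOS-2: "we hypothesized a clinically meaningful difference of 2 points in the intervention group compared to the control group".

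**The concern.** A treatment effect in a randomised trial is a difference between arms. Change within the VR arm mixes any VR effect with development, with the family intervention that both arms receive (section 2.8.2), and with regression to the mean. Calling that change a treatment effect invites the argument that VR works because its arm improved significantly, or because its arm did and the control arm did not. Neither inference has a controlled error rate.

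The between-group material does not settle the matter. A post-score t-test, a rank test chosen after a normality check, a time-by-group interaction and a group main effect could each be presented as the result. They differ in what they estimate and in power. The rank test need not address the 2-point mean difference used for planning. A two-level time factor also leaves open which visit counts as after, and it cannot by itself answer the sustainability question at weeks 24 and 32.

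**Working it through.** **Inputs from section 2.2.** "Previous studies reported an average ADOS-2 score of 16.9 ± 4.1 for children with ASD", so SD = 4.1; difference 2 points; "with the stipulation of α=0.05 and the test efficacy 1-β=0.8"; 72 before dropout, read as per arm because 72/0.9 = 80. Sidedness is not stated, and two-sided is assumed.

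**Assumptions not in the article.** Pre-post correlation r of ADOS-2, taken as 0.3 to 0.7; improvement common to both arms, taken as 1 point; equal SD before and after.

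**1. The plan's own figure.** n per arm = 2 × (1.960 + 0.842)² × 4.1² / 2² = 66 by the normal formula, or 67 by the t-test. The stated 72 is not reproduced, but it is larger. With 72 per arm the standard error of the unadjusted difference is 4.1 × √(2/72) = 0.683, and power is about 83%. The discrepancy is a separate, minor matter and does not affect this point.

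**2. Within-group test with no VR effect.** SD of change = 4.1 × √(2(1 − r)). The noncentrality is 1 / (SD of change / √72), on 71 degrees of freedom. Let p be the chance that the VR arm shows a significant improvement. The arms are independent, so the chance that VR is significant and control is not is p(1 − p).

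| r | SD of change | p | p(1 − p) |
|---|---|---|---|
| 0.3 | 4.85 | 41% | 24% |
| 0.4 | 4.49 | 46% | 25% |
| 0.5 | 4.10 | 53% | 25% |
| 0.6 | 3.67 | 63% | 23% |
| 0.7 | 3.18 | 75% | 19% |

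A two-sided 5% between-group test would favour VR falsely in 2.5% of trials.

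The result depends on the assumed common improvement. At r = 0.5, common gains of 0.5, 1, 1.5 and 2 points give p = 17%, 53%, 87% and 98%, and p(1 − p) = 14%, 25%, 12% and 2%.

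**3. Power of the between-group candidates for a true 2-point effect, 72 per arm.** The post score uses SD 4.1. The change score, which is the same test as the time-by-group interaction with two time levels, uses 4.1 × √(2(1 − r)). ANCOVA uses 4.1 × √(1 − r²).

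| r | Post score, unadjusted | Change score or interaction | ANCOVA |
|---|---|---|---|
| 0.3 | 83% | 69% | 86% |
| 0.4 | 83% | 76% | 89% |
| 0.5 | 83% | 83% | 92% |
| 0.6 | 83% | 90% | 95% |
| 0.7 | 83% | 96% | 98% |

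The group main effect of a two-by-two layout averages baseline with post-treatment, so it estimates 1 point rather than 2, with SD 4.1 × √((1 + r)/2). Its power is about 44% at r = 0.3 and 35% at r = 0.7. The article does not say it would be used; the figure shows only why the contrast must be named.

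**4. Visits.** Section 2.1 schedules five post-baseline assessments. Section 3 gives the time factor one post-baseline level and does not say which visit it is.

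**The case against.** The article frames the trial as a comparison of arms throughout. The hypothesis (section 1), the aim (section 2.1) and the sample size (section 2.2) all compare VR with control, and section 3 plans independent-sample t-tests and lists group as a factor. The usual reading of a time-and-group layout is the interaction, which is a valid between-group test. The unadjusted t-test is unbiased under randomisation and exceeds the planned 80% power. The false-positive figures describe a decision rule that the article does not state outright. How the later visits are modelled may be set out in an analysis plan that is not shown.

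Most of this stands, and it rules out several stronger readings that a reader might infer:

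- That efficacy is judged only within groups, or that the t-test is the only between-group test. Section 3 contradicts both.
- That baseline is ignored. Before is a level of the time factor, so an interaction test would use baseline as a change score. What is absent is baseline as a covariate.
- That four of the six visits are discarded. The t-tests are not restricted to two visits; the fault is a mismatch between the time factor and the schedule.
- That the absence of a centre term is an error. The abstract describes a "protocol for an initial multicenter randomized controlled trial", but silence on centre in a condensed article is not a fault.
- That the trial is underpowered. On its own inputs it is not.

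The objection does not remove the sentence that assigns treatment effects to within-group ANOVAs. That is a statement in the text, not an omission. Nor does it supply the missing choice among contrasts whose power differs widely.

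**Conclusion.** The point holds in this limited form. Section 3 labels a within-group analysis as the evaluation of treatment effects. It also leaves the efficacy contrast unidentified among between-group options that do not adjust for baseline as a covariate, one of which is selected by a normality test.

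The validity risk is conditional. If within-group results were read as efficacy, then under no VR effect and an assumed common 1-point gain, the VR arm would appear to benefit in about 41% to 75% of trials, and VR but not control would be significant in about 19% to 25%. These ranges cover assumed correlations of 0.3 to 0.7 and also move with the assumed gain.

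The efficiency loss is secondary. Against about 83% for the valid unadjusted test, ANCOVA gives 86% to 98%. The size of the gain depends on a correlation that the article does not give. ANCOVA also exceeds the change-score or interaction test at every correlation examined.

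**What to change.** Reword section 3 as follows.

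1. Delete the statement that treatment effects are evaluated within each group. Keep paired and other within-group tests as descriptive only.
2. Make the primary efficacy analysis the between-group difference in ADOS-2 at one named post-treatment visit, from an ANCOVA with baseline ADOS-2 as covariate. Fit it whatever a normality test shows, and report the adjusted difference with a 95% confidence interval.
3. Alternatively, fit a mixed model to all post-baseline visits with group, visit, group-by-visit and baseline ADOS-2 (by visit), and take the contrast at the named visit as primary. This also covers weeks 24 and 32 and removes the mismatch with the visit schedule.
4. Use the same form for the other continuous outcomes (CARS, ABC, SDQ and the Fisher-transformed fNIRS connectivity values), each with its own baseline.

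The cost is rewording. The baseline data are already collected, the named software fits both models, and no further participants or visits are needed. Section 2.4 gives the trial as recruiting with an anticipated end in September 2026, so the change can be made and dated before results are known.

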## Statistical analysis

3

The fNIRS data will be analyzed using the NirSpark software package developed by HuiChuang in China. During preprocessing, the first 20 s of each recording will be removed to eliminate signal instability and ensure data quality. Motion artifacts will be identified and corrected on a per-channel basis using spline interpolation, and a band-pass filter (0.01–0.20 Hz) will be applied to reduce interference from general physiological noise. Optical density data will be converted to oxygenated hemoglobin (HbO2) concentration values based on the modified Beer–Lambert law, using age-adjusted differential path length factors of 5.5, 5.2, and 4.6 as appropriate (35). After preprocessing, a resting-state functional connectivity analysis will be conducted to examine connectivity between brain regions. The resting-state data for each subject and time point will be extracted, and the oxygenated hemoglobin levels in each brain region’s time series will be quantified. Pearson correlation coefficients will be calculated for oxygenated hemoglobin across channels and brain regions to assess connectivity. These coefficients, represented as r values, will be used as indices of whole-brain resting-state functional connectivity. To normalize the distribution, Fisher’s z-transformation will be applied to the correlation coefficients (r), producing transformed Z-values that represent the strength of connectivity for each channel. This should allow for comparisons of relative connectivity strength ROIs. Ultimately, focusing on the eight ROIs of the cerebral cortex, their resting-state functional connectivity intensities were analyzed in depth to reveal the functional interactions between different brain regions.

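### Multiple imputation is the primary missing-data method, but a normality check picks the between-group test, and its nonparametric branch has no stated estimate to pool

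*Protocol article*

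**What the plan says.** All the relevant rules stand in one paragraph of the article's Statistical analysis section (Section 3).

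- Missing outcomes: "we will assume that data are missing at random and will apply multiple imputation as the primary approach".
- Between-group comparison if the measure is normal: "Independent sample t-tests will be employed for between-group comparisons of normally distributed measures".
- Otherwise: "nonparametric tests will be utilized for between- and within-group comparisons of non-normally distributed measures". No particular test or estimator is named.

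The paragraph does not exempt the primary outcome from this choice. Section 2.2 ties the sample size to the ADOS scale, using a 2-point difference and an SD of 4.1. No SAP is shown.

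**The concern.** Multiple imputation produces several completed data sets. Its standard combination, Rubin's rules, needs the same estimate and its standard error from each. A test chosen by a normality check does not guarantee that. Some imputed sets may pass the check and go to the t-test, while others fail and go to a rank test. A rank test, as the plan names it, returns a rank statistic and a p-value, with nothing to enter into the combination.

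At stake is whether the primary between-group result is fixed in advance. If the rank branch is reached, the analyst must add something that the plan does not contain: an estimator for that branch, a way of combining p-values, or a rule for split sets. Different additions can give different answers.

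**Working it through.** **1. The plan's sizing.** Inputs from Section 2.2: difference 2, SD 4.1, α = 0.05, power 0.80, 10% loss.

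n per group = 2(z₀.₉₇₅ + z₀.₈₀)²σ²/δ² = 2 × (1.960 + 0.842)² × 16.81/4 ≈ 66, or 67 with the t distribution. One-sided, it is 52–53.

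The published 72 is not reproduced. Multiplying 67 by π/3, a usual allowance for a rank test, gives 70.2, so 71; but Section 2.2 names no test. The last step does reproduce: 72/0.90 = 80 per group. For the present point, what matters is that the stated inputs are a mean difference and an SD.

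**2. What each branch gives for pooling.** With estimate Q and variance U from each of M imputed sets, Rubin's rules give the mean of the Q values and a total variance T = W + (1 + 1/M)B. Here W is the mean of the U values and B is the variance of the Q values.

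- *t-test branch.* Q is the mean difference and U its squared standard error. In 400 simulated trials (80 per arm, SD 4.1, true difference −2, 10% missing at random, baseline–outcome correlation 0.6, M = 20) the mean pooled estimate was −2.05 and the mean pooled standard error 0.67. The empirical SD of the estimates was 0.69, so this branch works as it should.
- *Nonparametric branch.* The plan states neither Q nor U, so T cannot be formed without adding an estimator.

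**3. How often the check splits the imputed sets.** The settings are those of step 2, with Shapiro–Wilk at 0.05 in each arm of each imputed set. The correlation, the skewness and the choice of normality test are assumptions, because the documents give none of them. The skewed outcome is 0.6 and 0.8 times two gamma variables of skewness 1, so its skewness is 0.6³ + 0.8³ = 0.73.

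| Scores | Sets disagree on the test | All sets to t-test | All sets to rank test | At least one set to rank test |
|---|---|---|---|---|
| Normal | 29.25% | 69.25% | 100 − 29.25 − 69.25 = 1.5% | 100 − 69.25 = 30.75% |
| Skewness 0.73 | 36.25% | 6.25% | 100 − 36.25 − 6.25 = 57.5% | 100 − 6.25 = 93.75% |

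Other simulations with the same arm size, missingness and correlation (300 trials per setting) gave disagreement of 39–54% at skewness 0–0.5 and 40–62% at 0–0.6. At skewness 1 they gave 5–8%, because nearly every set then goes to the rank test. A run with integer scores gave 29–56% over skewness 0 to 1. The figure at high skewness therefore depends on how the skew is generated.

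**4. Is the rank branch a real possibility for ADOS-2?** Section 2.7.5 describes a score built from items rated 0 to 2, and Section 2.3 requires a total above 7. That cut-off lies (16.9 − 7)/4.1 = 2.4 SD below the mean, so it would create little skew by itself. Even so, with exactly normal scores at least one of 20 sets failed the check in about 31% of trials.

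**5. Effect on the decision.** In simulated imputed sets the t-test and the rank test gave the same decision at 0.05 in 90–95% of cases, so they differed in 5–10%.

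**The case against.** The best defence is that a journal article may leave the imputation model, the pooling rule and the data used for the normality check to a SAP. That stands: their absence alone is no finding. But the article does not merely omit; it commits to a data-dependent test together with imputation as primary. A SAP can repair this only by removing the switch or by adding an estimator to the rank branch.

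It is also fair that Section 2.5 has the final analysis done by a statistician blinded to allocation. That limits any choice favouring one arm, but it does not define the pooled estimate.

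Four stronger readings are tempting, and the documents do not support them.

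- *That none of the named methods can be pooled.* The independent t-test pools directly, and so does the paired one ("Paired-sample t-tests will be employed to assess for pre- and post-treatment comparisons between normally distributed measures"). Kappa has a large-sample standard error and is reserved for something else: "the Kappa consistency test will be used to perform pre- and post-comparisons of count data". The repeated ANOVA is described with "The factors considered include time (before and after) and group (experimental vs. control), with each measure serving as a dependent variable". With two times and two groups the interaction has one degree of freedom and equals a t-test on change: in a numerical check F and t² were both 7.276.
- *That the plan can never give a single primary result.* If ADOS-2 passes the check in every imputed set, it does.
- *That imputed sets falling on both sides of p = 0.05 measure the defect.* With one fixed t-test and no switch this happened in 35–38% of simulated trials at a 1.4-point difference, against 36–39% with the switch. At 2 points and skewness 0.5 it was 23% against 22%. It is ordinary between-imputation variation.
- *That fNIRS makes imputation unworkable.* Eight regions give 8 × 7/2 = 28 pairs, and six visits would give 168 variables. But the Introduction and Discussion describe fNIRS as a pre- and post-intervention measure (28 × 2 = 56), and no single joint imputation model is stated.

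**Conclusion.** The concern holds in a limited form. Imputation as the primary approach does not fit with a normality-chosen test for the primary outcome, because one branch has no stated estimate to pool and the branch need not be the same in every imputed set. The pooled primary result is undefined only if ADOS-2 fails the check in some or all sets. Disagreement between sets arose in roughly 29–60% of simulated trials at low to moderate skewness. At higher skewness most or all sets may go to the rank test, which has nothing stated to pool. These rates rest on a correlation of 0.6, 20 imputations, 10% missing and a Shapiro–Wilk check; only the 10% comes from the plan.

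Nothing here shows bias or a wrong choice of missing-data assumption, and the two tests usually agree. It should be settled before the data are analysed. Section 2.4 gives the trial as recruiting, with an anticipated end of 30 September 2026.

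**What to change.** For ADOS-2, remove the normality-based choice and state one estimator. Suggested wording for the SAP:

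> The primary estimate is the between-group difference in mean ADOS-2 at the designated primary visit, adjusted for baseline ADOS-2, whatever any normality test shows. Missing values are multiply imputed within arm from baseline and the other visits. The same linear model is fitted in every imputed data set, and estimates and standard errors are combined by Rubin's rules. A rank test is a sensitivity analysis, with its method of combination stated.

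A likelihood-based mixed model on all observed ADOS-2 visits is an alternative under the same missing-at-random assumption and needs no imputation. Either choice matches the 2-point mean difference and SD of 4.1 used for sizing.

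The cost is wording only: no added children, visits or measurements, since baseline ADOS-2 is already collected. Adjustment should also gain precision. With 72 completers per arm the unadjusted standard error is 4.1 × √(2/72) = 0.68. Multiplying by √(1 − ρ²) gives about 0.63, 0.55 or 0.41 for assumed baseline correlations ρ of 0.4, 0.6 or 0.8.
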